#### Follow-up

All baseline measures will be repeated at the follow-up time point, 2 months postrandomisation. In addition, those in the intervention arm will be asked about their use of the programme, and their views on the content and design. Those in the control arm will be asked whether they had access to MoodHwb, to explore contamination. A subgroup of YP (n=up to 20–25) and parents/carers (n=up to 10–15) who used the programme will be interviewed at follow-up on their use of and views of MoodHwb and the evaluation process. The Web/app usage of those using the programme will be monitored using Google Analytics up to 6 months postrandomisation, to provide information on longer-term use. There will be a focus group for professionals who work with YP from a range of settings, to ascertain their views.

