### Sample size

We aim to recruit up to 120 adolescent participants and their parents/carers. Approximately two-thirds of the participants will be from Wales and one-third from Scotland. We expect a dropout of around 30%, based on previous digital health studies and the development and early evaluation work. With a sample size of 120 we can estimate the overall expected retention rate of 0.7 to within ±0.082 (70%±8.2%).

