### Assessment schedule

Data will be collected at (1) baseline and (2) follow-up, 2 months after randomisation. Data will be collected from (1) baseline and follow-up online questionnaires; (2) semistructured interviews with YP and parents/carers who used the programme; (3) a focus group with professionals and (4) Web/app usage data (table 1).

**Table 1 T1:** Schedule of enrolment, interventions and assessments for the trial

Time point	Screening (contact 1)	Baseline (contact 1)		Month 2 (contact 2)	
Activity		Intervention	Control	Intervention	Control
Referral to the trial/register of interest	X				
Eligibility assessment	X				
Consent process	X				
Randomisation	X				
Access to MoodHwb		X			
Questionnaires					
Adolescent Depression Knowledge Questionnaire^34^		·/○	·/○	·/○	·/○
Depression Stigma Scale^35^		·/○	·/○	·/○	·/○
General Self-Efficacy Scale^36^		·	·	·	·
General Health-Seeking Questionnaire^37^		·	·	·	·
Warwick-Edinburgh Mental Well-being Scale^31^		·/○	·/○	·/○	·/○
Mood and Feelings Questionnaire^24^		·/○	·/○	·/○	·/○
Revised Children’s Anxiety and Depression Scale-Short Version-25^38^		·/○	·/○	·/○	·/○
Hospital Anxiety and Depression Scale^39^		○	○	○	○
Items on health economics and life events^40^		·/○	·/○	·/○	·/○
Items on use and acceptability of MoodHwb				·/○	
Process evaluation					
Young person interview (n=20–25)				·	
Parent/carer interview (n=10–15)				○	
Professionals focus group				*	

(·Participant/○ parent/*professionals) ‘contact’ will comprise phone/videoconferencing discussion and completion of online forms/questionnaires.

We will use remote methods for recruitment, consent and data collection (eg, phone, email, videoconferencing, online forms and questionnaires) because these have been shown to be efficient and effective ways of conducting research during the COVID-19 pandemic. This approach is consistent with the digital nature of the programme and would enable us to reach more YP. All participants will be offered £10 gift vouchers after (1) completing baseline questionnaires, (2) completing follow-up questionnaires and (3) participating in interviews.

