### Outcome measures

#### Primary outcome

The feasibility and acceptability of MoodHwb outcomes will include the level of usage and adherence (including number of times accessed and duration of use), views and acceptability of the design and content (including strengths, areas to develop further and approaches to integrate into services and charities), and technical and accessibility aspects. The feasibility and acceptability outcomes of the trial methods will include recruitment and retention rates, completeness of measures, representativeness, randomisation, contamination and acceptability (particularly of the remote methods). Progression criteria for a full trial have been developed with the TSC, based on these outcomes (online supplemental appendix 1).

10.1136/bmjopen-2022-070369.supp1Supplementary data

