### Strengths and limitations

MoodHwb was codesigned with YP with lived experience or at high risk of depression, parents/carers and practitioners. The programme is bilingual, interactive, personalised according to user needs and preferences, and multiplatform. It has been developed in line with evidence-based approaches, not only for YP but also for those concerned about them. Multiple methods will be used to collect data in a range of settings, including validated questionnaires, semistructured interviews, a focus group and Web/app usage monitoring. The involvement of participants in the second site in Scotland will help to boost recruitment and enable the exploration of transferability.

Given that this is a feasibility study, we will not be able to explore effectiveness; however, the information and experience will inform the design of a future effectiveness trial. While it is not feasible to blind participants to allocation; data analysis will be carried out blind to allocation. We have minimised the risk of contamination between trial arms by ensuring that a log-in is required to access MoodHwb. There will be items in the follow-up questionnaire for participants in the control arm on whether they have accessed MoodHwb during the study.

Having access to the internet and an email address is one of the inclusion criteria for the trial, however, some participants might not be adept at using digital devices (eg, mobiles, desktop computers), or might prefer other approaches (eg, face to face, printed). This might affect adherence to the digital programme and retention in the study, and we will explore methods of engaging participants during the study, for example, via questionnaires and interviews.

At the end of the study, there will be a period of reflection and planning regarding what further development, evaluation and implementation work are required for MoodHwb, both as a standalone and supported technology, in collaboration with YP. If it is ultimately found to be feasible and effective, it could be rolled out to help YP, families/carers and practitioners across a range of settings.

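### The questionnaire rating of MoodHwb's acceptability is taken only at 2 months and summarised in complete cases, so about 24 of the 80 young people allocated to MoodHwb would not be represented in this part of the primary outcome

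*Protocol article*

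**What the plan says.** Acceptability of the programme is part of the primary outcome. The Primary outcome section lists "views and acceptability of the design and content" alongside usage, adherence and technical aspects, and says that progression criteria, held in a supplement, rest on these outcomes.

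The timing is fixed in two places. The Table 1 row "Items on use and acceptability of MoodHwb" is marked under month 2 in the intervention arm only, for young people and parents. The Follow-up section agrees: "In addition, those in the intervention arm will be asked about their use of the programme, and their views on the content and design". The acceptability items at baseline concern the questionnaires, not MoodHwb. The article describes no earlier, in-programme or exit rating.

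On loss, the Sample size section states: "We expect a dropout of around 30%, based on previous digital health studies and the development and early evaluation work". The section on participant and web usage data limits every summary after the baseline demographics to complete cases, within randomised groups. The Quantitative analysis section plans one check for drop-out bias: a table of baseline data for those who do and do not complete the study.

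The Strengths and limitations section says that some participants may not be adept with digital devices or may prefer another format, and adds: "This might affect adherence to the digital programme and retention in the study".

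**The concern.** A rating taken once, at the visit where loss is expected, and then summarised in those who answered, describes the responders and not the arm. That would matter little if loss were unrelated to how the programme suited people. The article gives a reason to think it may be related: it names one set of characteristics that might lower both use of MoodHwb and staying in the study. If that is right, the missing ratings are less favourable on average and the complete-case figure is too high.

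The planned check cannot detect this. No opinion of MoodHwb exists at baseline, so a baseline comparison of completers and non-completers says nothing direct about what the non-completers thought of the programme.

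At stake is how one component of the primary outcome is read when a definitive trial is being considered.

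**Working it through.** **Inputs**
- Maximum sample 120 and dropout about 30% (Sample size).
- Allocation 2:1 in favour of MoodHwb (Randomisation).
- Rating at month 2 only (Table 1; Follow-up).
- Complete-case summaries (Participant and web usage data).
- Assumed, because the article does not give them: 120 is reached, dropout is the same in both arms, and the approval rates below. The approval rates are illustrative only.

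**The plan's own figure.** The half-width of a 95% interval for retention of 0.7 with n = 120 is 1.96 × √(0.7 × 0.3 / 120) = 0.0820. This agrees with the stated ±0.082. The 95% level is my assumption, as the section does not name it.

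**How many ratings are missing**
- Allocated to MoodHwb: 120 × 2/3 = 80.
- Responding: 80 × 0.70 = 56.
- Not responding: 80 − 56 = 24.

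**Bounds for approval among all 80.** With y approving responders and m non-responders, the lower bound is y/80 (no non-responder approves) and the upper bound is (y + m)/80 (all approve).

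| Dropout | Responders / missing | Approval in responders | Lower | Upper |
|---|---|---|---|---|
| 30% | 56 / 24 | 45/56 = 80% | 45/80 = 56% | 69/80 = 86% |
| 30% | 56 / 24 | 39/56 = 70% | 39/80 = 49% | 63/80 = 79% |
| 20% (assumed) | 64 / 16 | 80% | 51.2/80 = 64% | 67.2/80 = 84% |
| 40% (assumed) | 48 / 32 | 80% | 38.4/80 = 48% | 70.4/80 = 88% |

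**A less extreme case.** The error in the responder figure is the fraction missing times the difference between responders and non-responders. If non-responders rate the programme 20, 30 or 40 points lower (assumed), the error is 0.30 × 20 = 6, 0.30 × 30 = 9 or 0.30 × 40 = 12 points.

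**Comparison with sampling error.** For 80% approval in 56 responders, the 95% half-width is 1.96 × √(0.8 × 0.2 / 56) = 0.105, or about 10 points. An error of 6 to 12 points is therefore of similar size, and a confidence interval computed in responders would not reflect it.

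**Do other sources fill the gap?**
- Interviews take place at the same follow-up, with people who used the programme, selected as frequent or occasional users. Young people lost to the study are not a sampling category.
- Parents also answer the items, but at the same time point, and they give their own view.
- Usage logs do not depend on returning a questionnaire and run to 6 months, but they record behaviour and not opinion.

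**The case against.** The case for leaving the plan alone is substantial.

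- **Stopping use is not the same as being lost.** A reader might infer that anyone who abandons MoodHwb early is never asked. The documents do not support that: the whole intervention arm is asked at 2 months, with phone or video contact and a voucher for completing follow-up. Only young people lost to follow-up are missed. This stands.
- **Upward bias is not shown.** A reader might infer that the missing people are those who disliked the programme. The article says only that digital fit or preference might affect adherence and retention. It gives no reasons for the 30% and no split by arm. This stands: the direction is plausible, not established.
- **No acceptability percentage is defined.** The component is partly qualitative and draws on questionnaires, interviews and a focus group together. This stands, so the fix is worded for any proportion that is reported. It is also true that the bounds are as wide as the missing fraction in any study. They measure the uncertainty but are no evidence of bias.
- **The effect on progression is unknown.** A reader might infer that the trial could progress wrongly. The criteria are in a supplement that is not shown, so neither a threshold nor its effect can be assessed.
- **There are safeguards.** Retention is reported beside acceptability, usage is logged independently, and occasional users are interviewed. These help with interpretation, but none gives the views of young people lost to follow-up.
- **This is analysis-plan detail.** Denominators are often left to an analysis plan, and exit questions to a full protocol that is not shown. That would decide the matter if the article were silent on handling. It is not: it fixes both the time point and the complete-case rule, and the point concerns those stated choices.

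**Conclusion.** The point holds in a limited form. As written, the young people's questionnaire rating of MoodHwb would describe about 56 of 80 allocated, and the stated drop-out check cannot show how the other 24 differ in their view. With an illustrative 80% approval among responders, the value for the whole arm is compatible with 56% to 86%. An overstatement of 6 to 12 points follows if non-responders are 20 to 40 points less favourable.

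These figures rest on reaching 120, on equal dropout of 30% in both arms, and on assumed approval rates. The direction of any bias is an inference from the article's own remark about adherence and retention. The usage and adherence components of the primary outcome are not affected in the same way, because the logs do not depend on the questionnaire. Collecting the rating at 2 months is defensible. The weakness is summarising it in complete cases alone, and that can be remedied cheaply in reporting.

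**What to change.** 1. For any acceptability proportion from the questionnaire, report beside the complete-case figure the number of young people responding out of all those allocated to MoodHwb, with lower and upper bounds obtained by counting all non-responders as not approving and then as approving.
2. In the MoodHwb arm, extend the planned comparison of completers and non-completers from baseline data to the usage data already being collected. This needs usage that can be linked to individuals. The article does not say so outright, though a log-in is required.
3. Interpret the acceptability results against both sets of figures.

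The cost is a little more analysis and a wider, less favourable stated range. No new data collection is needed, so the change can be made after recruitment has ended.

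Two further steps may suggest themselves, and I would not take them. A rating prompt inside MoodHwb after first use would measure a first impression and not acceptability over 2 months, would still miss those who never log in, and would mean changing a bilingual app during recruitment. Applying a progression threshold to the bounded figure cannot be justified while the criteria are not in view.

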### Process evaluation

The interviews with YP and parents/carers at follow-up and practitioner focus group noted earlier will provide more in-depth information on the acceptability and feasibility of the programme and evaluation process—in addition to the questionnaire and Web/app usage data. Participants will be purposively selected for interview based on their usage of MoodHwb (ie, frequent or occasional), age, gender, support received (eg, school, health service) and primary language (English, Welsh)—so that there is a broad range of viewpoints. A process evaluation framework has been developed, following MRC guidance,^28^ and focuses primarily on the intervention but also examines certain trial processes. It addresses issues regarding reach, contamination, retention, recruitment, context, exposure and fidelity.

### Outcome measures

#### Primary outcome

The feasibility and acceptability of MoodHwb outcomes will include the level of usage and adherence (including number of times accessed and duration of use), views and acceptability of the design and content (including strengths, areas to develop further and approaches to integrate into services and charities), and technical and accessibility aspects. The feasibility and acceptability outcomes of the trial methods will include recruitment and retention rates, completeness of measures, representativeness, randomisation, contamination and acceptability (particularly of the remote methods). Progression criteria for a full trial have been developed with the TSC, based on these outcomes (online supplemental appendix 1).

10.1136/bmjopen-2022-070369.supp1Supplementary data

#### Secondary outcomes

Secondary outcomes assess the potential impact of the programme on a core set of domains, including depression literacy or knowledge, depression stigma, help-seeking behaviour, self-efficacy, well-being, and depression and anxiety symptoms. These will be measured via standardised validated questionnaires (table 1), and participant feedback (via questionnaires and interviews).

#### Exploratory economic evaluation

We will investigate the feasibility and acceptability of collecting health economic data. We will identify and measure the resources involved in intervention delivery as well as resource use by participants, with reference to methodology from health economics guidance.^29 30^ An estimation of the following will be collected: (1) intervention costs (development, hosting and maintenance costs), (2) health (eg, contact with GPs, hospitals and other health settings, medication), social, educational and personal resource costs, using questionnaire items adapted from the Client Service Receipt Inventory and (3) well-being, using the Warwick-Edinburgh Mental Well-being Scale.^31^

### Planned analysis

Primary outcome findings will be derived primarily from analysis of the questionnaires, interviews and focus group, with additional analysis of Web/app usage data regarding usage, adherence and technical aspects, and screening logs and participant database regarding recruitment and retention. Secondary outcome findings will be derived primarily from analysis of validated questionnaires.

#### Participant and web usage data

The flow of participants through the trial will be presented as a CONSORT (Consolidated Standards of Reporting Trials) flow chart.^32^ Baseline demographic data will be presented for all consented and randomised participants. This will be summarised and tabulated for the whole group and by arm, using mean (SD) or median (IQR) where appropriate. All subsequent summaries will use complete cases and will employ the intention to treat principle (participants will remain in groups to which they were randomised irrespective of intervention received). Web usage data from Google Analytics will be tabulated, for example, related to number of times accessed, duration of use, sections accessed and language.

#### Qualitative analysis

The interviews and focus group recordings will be transcribed, and data analysis will proceed using a thematic analysis approach. This is a process of identifying, analysing, reporting and interpreting patterns or themes, and is one of the most used qualitative approaches in health research.^33^ Codes will be applied to broad themes and then broken down further into subcodes—30% will be double-coded to ensure the reliability of coding, and differences will be resolved through discussion. Transcripts will be closely examined to identify key themes and subthemes. Thematic analysis will be supported by the computer-assisted qualitative analysis software, NVivo.

#### Quantitative analysis

Baseline questionnaire data will be scored according to the validated scoring algorithms from the relevant literature. Missing item-by-item data will be handled according to the scoring algorithm for each measure individually. Baseline scores will be presented descriptively, using summary statistics (means, SD, medians, IQR and percentages with associated 95% CI where appropriate) for the whole group and by arm. Distributional assumptions will be checked, and data transformation carried out if required. A comparison of randomised groups will be tabulated but not tested, in line with the feasibility aims. A comparison of baseline data for those completing and not completing the study will be tabulated to assess drop-out bias.

Scores at the 2-month time point will be tabulated and compared in a complete case analysis. No hypothesis tests will be carried out but 95% CI for the difference at 2 months between the two arms will be estimated and reported. These will be adjusted for baseline score and any factors such as site used to balance the randomisation. Statistical analysis will be performed using Stata software (version 17), but no p values will be presented. We will further develop and test the MoodHwb logic model (figure 2) using multiple methods, and examine possible mechanisms of action and active components. This will help to define a core set of outcome measures (related to the model) and identify the most appropriate primary outcome for evaluation in an effectiveness trial.

### Trial management

A trial management group (TMG) and an independent TSC have been established to monitor progress and advise the researchers. The TMG will meet approximately every 8–10 weeks during the trial planning and throughout the trial. The TMG is composed of the PI, coinvestigators, research assistant, trial administrator, CTR members and University of Glasgow site team. The TSC will meet approximately every 12 months. The TSC includes a young person, and an independent digital mental health researcher, statistician and mixed-methods researcher.

### Adverse event reporting and harms

For this trial, adverse events (AEs) are defined as any untoward medical occurrence in a participant administered an intervention and which are not necessarily caused by or related to that intervention. This would include significant deterioration in mental health symptoms, including depressive and anxiety symptoms, and emergence of thoughts of self-harm. Serious AEs (SAEs) include those resulting in death, are life-threatening, require hospitalisation or prolongation of existing hospitalisation, result in persistent or significant disability or incapacity, or other medically important conditions. The PI will assess each SAE for expectedness. A standard study/departmental procedure for documenting and dealing appropriately with these events will be followed. YP and parents/carers will be signposted to appropriate resources and services if there are concerns at the screening stage (see the Recruitment section) or from the questionnaire or interview responses if recruited. Their GP details will be collected at the screening and baseline stages, so they can be contacted. This is especially important, as the study will recruit self-referrals who might not access other support. An urgent safety measure is an action that the sponsor or PI may carry out to protect the participants of a trial against any immediate hazard to their health or safety—and must be notified to the REC immediately.

### Ethics and dissemination

Approvals were received from the Cardiff University School of Medicine REC and University of Glasgow College of Medical, Veterinary and Life Sciences REC for the pretrial acceptability phase with YP. Favourable ethical opinion for the overall study and trial was obtained from Wales REC 3 (reference 21/WA/0205), and approvals were received by HRA, HCRW, university health board R&D departments in Wales, and schools in Wales (including via SHRN) and Scotland (including via SHINE). The study was registered with ISRCTN (ISRCTN12437531). Approvals were received for MoodHwb to be added to the (Apple) App Store and Google Play App Store.

We will disseminate our findings to academics, researchers, policy-makers and practitioners through high-impact open-access publications and presentations at relevant academic, clinical and educational conferences and meetings. The findings will be disseminated online, for example, on the NCMH, WCYPMH and TRIUMPH websites. Results will be made available to all participants after the study completion.

